# Efficacy and safety of adjuvant transarterial chemoembolization in high-risk HCC after curative hepatectomy: a phase III RCT protocol

**DOI:** 10.1016/j.iliver.2026.100236

**Published:** 2026-04-25

**Keywords:** Adjuvant, Hepatocellular carcinoma, High-risk recurrence factors, Transarterial chemoembolization

## Abstract

**Introduction:**

Hepatocellular carcinoma (HCC) remains associated with a high risk of recurrence, with 5-year recurrence rates approaching 70% after curative hepatectomy. The Chinese Liver Cancer Staging guideline strongly recommend transarterial chemoembolization (TACE) as an adjuvant therapy to reduce postoperative recurrence and improve overall survival. However, its clinical benefit remains controversial, as guidelines from other regions do not support routine use of adjuvant TACE. This discrepancy may reflect the possibility that adjuvant TACE primarily facilitates detection of intrahepatic residual lesions through digital subtraction angiography (DSA), rather than conferring direct therapeutic benefit from embolic or chemotherapeutic agents.

**Methods and analysis:**

This multicenter, phase III randomized controlled trial will enroll 442 eligible participants, who will be randomly assigned in a 1:1 ratio to either an adjuvant TACE group or an intensive follow-up group. The primary endpoint of this study is to investigate whether adjuvant TACE could improve recurrence-free survival (RFS) in high-risk HCC patients following curative hepatectomy. The key secondary endpoints include the safety and tolerability of adjuvant TACE, as well as the effects of adjuvant TACE versus intensive follow-up on overall survival, median RFS, and time to tumor recurrence. This trial may addresses the critical clinical controversy regarding adjuvant TACE by excluding patients with residual tumor staining on DSA, to ensure genuine curative resection. The results will deliver high-quality evidence to clarify the efficacy and safety of adjuvant TACE, and standardize postoperative adjuvant strategies.

## Abbreviations

AEsAdverse eventsCNLCChinese Liver Cancer Staging Guidelines; CRFs, Case report formsCTComputed tomography; DSA, Digital subtraction angiographyECGElectrocardiogramECOG PSEastern Cooperative Oncology Group performance statusGCPGood Clinical PracticeHBVHepatitis B virusHCCHepatocellular carcinomaHCVHepatitis C virusMRIMagnetic resonance imagingOSOverall survivalRCTRandomized controlled trialRECISTResponse Evaluation Criteria in Solid TumorsRFSRecurrence-free survivalSAEsSerious adverse eventsTACETransarterial chemoembolizationTRAEsTreatment-related adverse events

## Introduction

1

Hepatocellular carcinoma (HCC) is characterized by an insidious onset and limited detectability at early stages, with approximately 70% of patients diagnosed at intermediate or advanced disease stages. Consequently, a substantial proportion of patients are no longer candidates for curative surgical resection and must rely on non-surgical locoregional therapies and systemic antitumor treatments.^1^ Hepatectomy and local ablation remain the principal curative approaches; however, postoperative recurrence continues to represent a major clinical challenge. The 5-year recurrence rate following curative hepatectomy approaches 70%, significantly limiting long-term survival outcomes.^2^^,^^3^ Moreover, even among patients with recurrent HCC who meet the Milan criteria, the 5-year recurrence rate after repeat curative resection remains similarly high.^4^, ^5^, ^6^ These findings reveal the critical importance of effective adjuvant strategies to reduce recurrence and improve overall survival (OS) after curative hepatectomy.^7^^,^^8^

A variety of adjuvant treatment strategies for HCC have been reported to date; however, the recommendations regarding adjuvant therapy remain inconsistent across international HCC guidelines. Although adoptive immunotherapy has shown modest benefit, its implementation is complex and thus is not routinely applied in clinical practice.^9^^,^^10^ By contrast, antiviral therapy for hepatitis B virus (HBV)-related HCC has achieved broad consensus, with multiple studies confirming both short- and long-term clinical benefits.^11^^,^^12^ Postoperative adjuvant therapy with PD-1 inhibitors has shown potential to improve recurrence-free survival (RFS) in selected patient subgroups,^13^, ^14^, ^15^, ^16^ but large-scale randomized controlled trials (RCTs) are still necessary to further confirm its efficacy, safety, and optimal patient selection.

The Chinese HCC guidelines additionally recommend adjuvant approaches including antiviral therapy, Huaier granules, and transarterial chemoembolization (TACE).^17^ Accordingly, many liver surgery centers in China have adopted 1–3 cycles of postoperative TACE in patients with high-risk recurrence features.^18^^,^^19^ By contrast, major international guidelines, including those from the American Association for the Study of Liver Diseases,^20^ European Association for the Study of the Liver,^21^ European Society for Medical Oncology,^22^ Barcelona Clinic Liver Cancer group,^23^ British Society of Gastroenterology,^24^ Asian Pacific Association for the Study of the Liver,^25^ and national guidelines from Republic of Korea,^26^ Japan,^27^ and Republic of India,^28^ do not recommend routine adjuvant TACE following curative resection.

The Chinese Liver Cancer Staging (CNLC)^29^ guideline strongly recommends adjuvant TACE after curative hepatectomy, largely based on two RCTs published in 2018.^30^^,^^31^ However, these studies did not specify whether patients with tumor staining on hepatic arteriography were excluded.^30^^,^^31^ Similarly, a recent retrospective analysis reported improved RFS and OS with postoperative TACE in selected patients with intermediate-to advanced-stage HCC and microvascular invasion, although patients with intraparenchymal tumor staining during TACE were not excluded.^32^ Advances in imaging further complicate interpretation of these findings. Historically, many patients underwent preoperative contrast-enhanced computed tomography (CT) without magnetic resonance imaging (MRI), whereas contrast-enhanced MRI now enables improved detection of intrahepatic microlesions, facilitating more complete resection. Notably, a recent RCT in patients with American Joint Committee on Cancer TNM stage I/II HCC demonstrated no RFS benefit with adjuvant TACE after curative hepatectomy.^33^

The TACE procedure begins with digital subtraction angiography (DSA), which can identify residual intrahepatic lesions through tumor staining that were not detected on preoperative imaging. The presence of tumor staining indicates that the criteria for standard curative hepatectomy may not have been fully met. However, prior studies^30^^,^^31^ have not accounted for this factor in their inclusion criteria, potentially contributing to the reported efficacy of adjuvant TACE. To further investigate this issue, we reviewed adjuvant TACE data from our center. Among 1390 patients who underwent curative hepatectomy between June 2019 and December 2023, 433 (31.1%) received adjuvant TACE 4–8 weeks postoperatively. Of these, 118 patients (27.3%) exhibited intrahepatic tumor staining on DSA, and these were the cases that actually benefited from postoperative TACE.^34^ These findings suggest that the apparent benefit of adjuvant TACE may primarily arise from detection of residual disease via DSA, rather than from the intrinsic therapeutic effects of embolization or chemotherapeutic agents.

In this context, this study is designed as a rigorously conducted multicenter phase III RCT that emphasizes truly curative resection and excludes patients with intraoperative tumor staining detected by DSA. The trial aims to evaluate the effect of adjuvant TACE on RFS in HCC patients with high-risk recurrence factors (Fig. 1). The findings of this study are expected to clarify the clinical value of adjuvant TACE, provide high-level evidence for precision treatment strategies and optimize resource utilization in HCC management.

**Fig. 1 fig1:**
[figure not shown]
Overview of the study design and participant flow.

## Methods

2

### Objectives

2.1

This study is a multicenter phase III RCT, aims to rigorously evaluate the clinical efficacy of adjuvant TACE of HCC patients with high-risk recurrence factors following curative hepatectomy. The primary endpoint of this study is to investigate whether adjuvant TACE could improve RFS in high-risk HCC patients following curative hepatectomy. The key secondary endpoints include the safety and tolerability of adjuvant TACE—such as incidence of treatment-related adverse events (TRAEs) and serious adverse events (SAEs), and the rate of treatment discontinuation attributable to TRAEs or SAEs—as well as the effects of adjuvant TACE versus intensive follow-up on OS, median RFS, and time to tumor recurrence.

RFS is defined as the interval from randomization to the first imaging-confirmed recurrence of HCC—whether intrahepatic or extrahepatic—or death from any cause. TRAEs is defined as any unfavorable or unintended medical occurrences following informed consent, irrespective of causality. SAEs is defined as events that result in death, are life-threatening, require hospitalization or prolong hospitalization, result in persistent or significant disability, cause congenital anomalies, or represent other medically significant conditions. OS is defined as the time from randomization to death from any cause; time to recurrence, defined as the interval from curative hepatectomy to first imaging-confirmed recurrence.

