### Informed consent

2.5

Written informed consent will be obtained from each participant or their legally authorized representative prior to initiation of any study-specific procedures. Participants will be fully informed of the study objectives, procedures, potential risks and benefits, alternative treatment options, data confidentiality measures, and their right to withdraw at any time. Adequate time will be provided for questions and consideration. The investigator or designated study personnel will document consent by signature and date, retain the original signed form at the study site, and provide a copy to the participant.

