### Interventions

2.8

All enrolled participants will undergo hepatic arteriography 4–8 weeks following curative hepatectomy. With the patient in the supine position, standard aseptic preparation and sterile draping of the right groin will be performed. After local anesthesia with 5 mL of 2% lidocaine at the right femoral artery puncture site, a 5F arterial sheath will be inserted using the Seldinger technique. A 5F hepatic catheter will then be advanced into the celiac trunk for angiographic assessment. The hepatic arterial system, including the left and right hepatic artery branches, will be systematically evaluated to identify intrahepatic tumor staining. Detection of one or more foci of tumor staining will indicate that the initial hepatectomy did not meet criteria for curative resection, and such patients will be excluded. Participants without evidence of tumor staining will be randomly assigned to either the adjuvant TACE group or the intensive follow-up group.

In the adjuvant TACE group, superselective catheterization will be performed targeting the hepatic resection margin, followed by embolization using an emulsion of 50 mg lobaplatin and 3–5 mL ethiodized poppyseed oil. This regimen is based on prior RCTs demonstrating a reduction in postoperative HCC recurrence with adjuvant TACE.^30^^,^^31^ Polyvinyl alcohol embolic microspheres will not be utilized, as they are not part of the standard adjuvant protocol. In the intensive follow-up group, hepatic arteriography will be performed without administration of embolic or chemotherapeutic agents. Upon completion of the procedure, the catheter and arterial sheath will be removed, and manual compression will be applied to achieve hemostasis. Adjuvant TACE will be administered as a single session only.

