i Thyroid function tests and cardiac enzyme panels will be performed within 28 days prior to first treatment, prior to each treatment cycle (from Cycle 2 onward), and during safety follow-up at study sites.

j Virological testing includes human immunodeficiency virus, HCV antibody, and hepatitis B panel (HBsAg, HBsAb, HBcAb, HBeAg, HBeAb), performed within 28 days prior to first treatment during screening.

k For participants with positive HCV antibody, HCV-RNA viral load will be assessed every (21 ± 7) days from first treatment or earlier if clinically indicated.

l For participants with positive HBsAg and/or HBcAb, HBV-DNA viral load will be assessed every (21 ± 7) days from first treatment or earlier if clinically indicated.

m Adverse events and laboratory safety parameters will be evaluated according to Common Terminology Criteria for Adverse Events version 5.0. Definitions, grading, causality assessment, reporting timelines, and management procedures are specified in Section 8 of the protocol.

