#### Adverse event reporting

2.17.2

Adverse events (AEs) will be graded according to the Common Terminology Criteria for Adverse Events (version 5.0). All AEs and SAEs will be comprehensively documented, including event type, onset and resolution dates, severity, relationship to the study intervention, and concomitant treatments. In addition to institutional reporting requirements, investigators must notify the principal investigator and the institutional ethics committee within 24 hours of becoming aware of any SAE. Participants will be followed until resolution of the event or return to baseline clinical status.

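### Section 2.1 gives the treatment-related adverse event endpoint the definition of an all-cause adverse event, so its label and its content contradict each other

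*Protocol article*

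**What the plan says.** All references are to the protocol article.

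- **Safety endpoint.** Section 2.1 lists among the key secondary endpoints the "incidence of treatment-related adverse events (TRAEs) and serious adverse events (SAEs), and the rate of treatment discontinuation attributable to TRAEs or SAEs".
- **Its definition.** The next paragraph of Section 2.1 states: "TRAEs is defined as any unfavorable or unintended medical occurrences following informed consent, irrespective of causality".
- **Causality elsewhere.** Section 2.17.2 requires each adverse event to be documented with its "severity, relationship to the study intervention, and concomitant treatments". Table 1, note m, says: "Definitions, grading, causality assessment, reporting timelines, and management procedures are specified in Section 8 of the protocol".
- **Consent.** Section 2.5 places consent "prior to initiation of any study-specific procedures". Table 1 puts it in the screening period, days −28 to −1, with TACE on day 1.
- **Time origins.** Section 2.1 starts RFS and OS at randomization, but gives "time to recurrence, defined as the interval from curative hepatectomy to first imaging-confirmed recurrence". Sections 2.6 and 2.6.1 place randomization after an angiogram without staining, done 4–8 weeks after surgery.
- **Treatment.** Section 2.8 states: "Adjuvant TACE will be administered as a single session only". The follow-up arm has the angiogram but receives no embolic or chemotherapeutic agent.

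**The concern.** A treatment-related event is a subset of adverse events, picked out by a causality judgement. Section 2.1 sets that judgement aside and starts the count at consent, so the endpoint as defined is the full set of adverse events. An analyst who follows the text would report all-cause events under a treatment-related heading, in both arms. For an adjuvant procedure whose value is disputed, the toxicity rate is one of the results readers will quote, and it would not mean what its name says. The discontinuation endpoint inherits the problem, because it is unclear what it means to attribute stopping to a treatment-related event when relatedness has been set aside.

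Two smaller points sit in the same section. Time to recurrence runs on a different clock from RFS and OS, so its absolute times cannot be read beside theirs. And a rate of stopping treatment has little content when the treatment is one session.

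**Working it through.** **1. Treatment-related events: the texts side by side.** The article gives no adverse event rates, so no arithmetic applies.

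| Source | Role of causality | Start of counting |
|---|---|---|
| Section 2.1, endpoint name | Required | Not stated |
| Section 2.1, definition | Disregarded | Informed consent |
| Section 2.17.2 | Recorded for each event | Not stated |
| Table 1, note m | Assessed, under Section 8 of the full protocol | Not stated |

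The definition disagrees with the name and with both other places that mention causality. Applied literally, it takes in three groups of events that the name excludes:

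- Events between consent and the procedure, since consent comes first (Section 2.5, Table 1).
- Complications of the angiogram that both arms undergo (Section 2.8), even where TACE was never given.
- Events in either arm that the investigator judged unrelated.

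**2. Time to recurrence: size of the shift.** Inputs are the 4–8 week gap (Section 2.6.1) and the 16.1-month median RFS used for planning (Section 2.12), which serves only as a scale. I assume randomization takes place at the angiogram.

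- Months = weeks × 7 / 30.4375.
- 4 weeks: 28 / 30.4375 = 0.92 months; 0.92 / 16.1 = 5.7%.
- 8 weeks: 56 / 30.4375 = 1.84 months; 1.84 / 16.1 = 11.4%.
- A 16.1-month median from randomization reads as 16.1 + 0.92 = 17.0 to 16.1 + 1.84 = 17.9 months from surgery.

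**3. Time to recurrence: effect on the comparison of arms.** I simulated 442 patients, 1:1, with exponential event times (control median 16.1 months), 12 months' uniform accrual and 24 months' further follow-up. The surgery-to-randomization gap was uniform over 4–8 weeks. There were 3,000 runs per hazard ratio. Each data set was analysed from both origins with a two-sided 5% log-rank test.

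| True hazard ratio | Rejection, origin randomization | Rejection, origin surgery | Estimated hazard ratio (randomization / surgery) |
|---|---|---|---|
| 1.0 | 5.4% | 5.3% | 0.995 / 0.995 |
| 0.7 | 86.2% | 86.2% | 0.699 / 0.699 |
| 1.4 | 87.4% | 87.3% | 1.405 / 1.405 |

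The gap arises before allocation and has the same distribution in both arms, so it moves both curves together.

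**4. Discontinuation.** With one session (Section 2.8) there is no later treatment to stop. Section 2.9.1 allows up to a week between randomization and TACE, so an allocated session may be withheld or left incomplete. Only such cases can count.

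**The case against.** **The wording may be a slip, corrected elsewhere.** The sentence reads like a standard adverse event definition under the wrong abbreviation, and note m sends the reader to Section 8 of the full protocol, which is not shown. This stands as an explanation. It does not rescue the article: the definition is stated, not left out, and if Section 8 is right then Section 2.1 contradicts it.

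**All-cause counting is a legitimate safety comparison.** This stands. A reader might infer that counting unrelated events biases the contrast between arms. The documents do not support that: background events are expected equally in randomized arms, and an all-cause comparison is what I recommend below. The fault is the label. Because Section 2.17.2 records the "relationship to the study intervention", related events can still be separated.

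**The recurrence clock does no harm to the comparison.** This largely stands. A reader might infer immortal-time bias from the pre-randomization span. The span precedes allocation and is balanced by it, and the simulation shows no material change in rejection rate or hazard ratio. What remains is the shift in absolute times.

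**Discontinuation is not meaningless.** This also stands. A reader might infer that the endpoint is empty, but a session can be withheld in the week allowed by Section 2.9.1, and Section 2.6.3 names serious events and intolerance as grounds for stopping. Largely uninformative is the accurate description.

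**Conclusion.** The definition of treatment-related adverse events in Section 2.1 is wrong as written and should be corrected. It affects a named key secondary endpoint, not the primary one. The number of events that would be mislabelled cannot be estimated from the article. By definition, it is every adverse event after consent that is not judged related to the study intervention.

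The recurrence origin is a lesser inconsistency. It adds about 0.9–1.8 months to absolute times, or 6–11% of the 16.1-month planning median, with negligible effect on the between-arm test or hazard ratio. This rests on three assumptions: randomization at the angiogram, a gap spread evenly over 4–8 weeks, and a recurrence time distribution close to the RFS planning figure, with deaths not modelled separately. Section 2.9.1 could be read as placing randomization before the angiogram. That would change the gap slightly but not the conclusion, because randomization still follows surgery. The discontinuation wording is minor.

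**What to change.** In Section 2.1:

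1. Give the present definition to adverse events, and compare all-cause adverse events and SAEs by arm.
2. Define treatment-related adverse events as those judged related to the study intervention, using the field recorded under Section 2.17.2. State whether the angiogram counts as part of that intervention.
3. Report events with onset before randomization separately where timing allows. Section 2.8 reads as a single catheter session, so some angiogram events will appear only after randomization and cannot be separated by date.
4. Start time to recurrence at randomization, as for RFS and OS. If surgery is kept as the origin, use delayed entry at randomization.
5. Restate the discontinuation rate as allocated TACE not given or not completed because of an adverse event.
6. Check that Section 8 of the full protocol agrees.

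Items 1, 2 and 4 are changes of wording and use data the plan already needs. A reader might assume the whole repair needs no new data, but the article does not show this. Section 2.17.2 does not record relatedness to angiography and to TACE separately, and no field for an incomplete session is described. Item 5, and any split by procedure, may therefore need a small addition to the case report form. The changes are best made before unblinding.

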### Patients

2.6

Following hepatic angiography confirming the absence of intrahepatic tumor staining, eligible participants will be randomly assigned in a 1:1 ratio to either the adjuvant TACE group or the intensive follow-up group. In the adjuvant TACE group, participants will undergo a single session of TACE after confirmation of no tumor staining on hepatic arteriography, followed by standardized intensive follow-up. Participants allocated to the intensive follow-up group will receive routine surveillance only after hepatic angiography. Patients in both groups were followed until death or study termination. Key landmarks defining follow-up cessation included: disease progression (defined as HCC recurrence or metastasis), death, withdrawal of informed consent, initiation of a new antitumor therapy, or any other protocol-specified reason for treatment discontinuation.

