**Safety Monitoring and Survival**				
Adverse Event Assessment m	×	×	×	×
Subsequent Anti-tumor Treatment				×
Survival Status				×

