**Investigational Drug Administration**				
TACE		×		

Notes.

a Written informed consent must be obtained prior to initiation of any protocol-specified procedures.

b Prior antitumor treatment history includes all therapies administered for HCC, such as chemotherapy, radiotherapy, and surgical interventions.

c Vital signs include body temperature, pulse rate, respiratory rate, and blood pressure.

d Height will be measured only during the Screening Period. Body weight will be recorded prior to each treatment administration. If body weight varies by less than 10% from baseline (defined as the day of first study treatment), baseline weight will be used for dose calculations; otherwise, the weight measured on the day of treatment will be used.

e A 12-lead ECG will be performed during the Screening Period, prior to each treatment cycle beginning from Cycle 2, and during the safety follow-up period.

f Complete blood count includes red blood cell count, hematocrit, hemoglobin, platelet count, white blood cell count, and differential counts (lymphocytes, monocytes, neutrophils, eosinophils, and basophils). Blood biochemistry includes liver function parameters (total bilirubin, direct bilirubin, aspartate aminotransferase, alanine aminotransferase, γ-glutamyl transferase, albumin, total protein, alkaline phosphatase, lactate dehydrogenase, and creatine kinase), renal function markers (urea and creatinine), blood electrolytes (sodium, potassium, chloride, magnesium, calcium, phosphorus), amylase, and blood glucose. Urinalysis includes pH, urine protein, red blood cells, white blood cells, glucose, and specific gravity. Participants with urine protein ≥2+ at screening will undergo 24-h urine protein quantification. These assessments will be performed within 7 days prior to first treatment, prior to each subsequent cycle (from Cycle 2 onward), and during safety follow-up. All tests will be conducted at study sites.

g Coagulation profile includes prothrombin time and international normalized ratio. Assessments will be performed within 7 days prior to first treatment, prior to subsequent treatment cycles (from Cycle 2 onward), and during safety follow-up at each study site.

h Female participants of childbearing potential will undergo serum pregnancy testing within 72 hours prior to the first treatment administration. If urine testing is inconclusive, serum testing will be used for confirmation. All tests will be conducted at study sites.

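### Section 2.1 defines treatment-related adverse events as all-cause adverse events after consent, so this secondary safety endpoint is wrong as written

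*Protocol article*

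**What the plan says.** Section 2.1 (Objectives) lists the safety measures among the key secondary endpoints. They are "incidence of treatment-related adverse events (TRAEs) and serious adverse events (SAEs") and "the rate of treatment discontinuation attributable to TRAEs or SAEs".

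The next paragraph of the same section gives the definition: "TRAEs is defined as any unfavorable or unintended medical occurrences following informed consent, irrespective of causality".

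Four other places bear on how that definition would work:

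- **Consent.** Section 2.5 says "Written informed consent will be obtained from each participant or their legally authorized representative prior to initiation of any study-specific procedures". Note a to Table 1 says the same.
- **Randomization.** Section 2.6 says "Following hepatic angiography confirming the absence of intrahepatic tumor staining, eligible participants will be randomly assigned in a 1:1 ratio". Section 2.8 gives the same order.
- **Adverse event collection.** The Table 1 row "Adverse Event Assessment m" is marked in all four columns, including screening (days -28 to -1).
- **Causality data.** Section 2.17.2 requires each event to be documented, "including event type, onset and resolution dates, severity, relationship to the study intervention, and concomitant treatments". Note m to Table 1 refers to Section 8 of the full protocol, which is not shown, for definitions and causality assessment.

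**The concern.** The endpoint's name and its definition cannot both hold. A treatment-related event is one attributed to the treatment, but the definition sets attribution aside. What it describes is any adverse event.

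The counting window is also too early for a treatment-related measure. It opens at consent, before screening, and a participant is allocated only later. Something that happens in that interval cannot be an effect of TACE, yet under the definition it is a TRAE.

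Safety is part of the decision this trial is meant to inform. Section 2.7 presents avoidance of adverse effects as an advantage of the follow-up arm. Under the definition as written, controls, who receive no embolic or chemotherapeutic agent, would have a treatment-related rate equal to their background event rate. The TACE rate would mix background with toxicity. The discontinuation endpoint uses the same term, so a discontinuation caused by an unrelated event would also qualify as one due to a TRAE.

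**Working it through.** **Reading the text.** The article states no adverse event rate, safety sample size or safety power, so there is no figure of its own to reproduce. The check is first one of wording and sequence.

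1. Endpoint: incidence of treatment-related events (2.1).
2. Definition: any event after consent, whatever its cause (2.1). Unrelated events therefore count.
3. Sequence: consent, then screening, then angiography, then randomization (2.5, 2.6, 2.8). Adverse events are assessed at screening (Table 1). Events before randomization therefore count.
4. No other visible section corrects the definition. Section 2.17.2 supplies the fields needed for a true treatment-related subset but does not change the endpoint.

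One ambiguity remains. Section 2.9.1 speaks of up to one week between randomization and TACE, and of excluding participants in whom angiography shows staining. This can be read as allowing randomization before the angiogram. Consent and screening precede randomization on either reading.

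**Illustration of size (all rates assumed).** Let r be the probability of a TACE-caused event. Let b be the probability of an unrelated or pre-randomization event, equal in the two arms and independent of r.

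- Labelled TRAE proportion, TACE arm: 1 - (1 - r)(1 - b)
- Labelled TRAE proportion, control arm: b
- Apparent difference: r(1 - b)
- Excess of the TACE-arm figure over the TACE-caused risk: b(1 - r)

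With r = 30%:

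| b | TACE arm | Control arm | Apparent difference | TACE-arm excess over r |
|---|---|---|---|---|
| 10% | 37% | 10% | 27 points | 7 points |
| 20% | 44% | 20% | 24 points | 14 points |
| 40% | 58% | 40% | 18 points | 28 points |
| 50% | 65% | 50% | 15 points | 35 points |
| 70% | 79% | 70% | 9 points | 49 points |
| 90% | 93% | 90% | 3 points | 63 points |

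For example, at b = 10%: 1 - 0.70 × 0.90 = 0.37, and 0.37 - 0.10 = 0.27.

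Varying r from 20% to 50% and b from 10% to 40%, the TACE-arm figure exceeds the TACE-caused risk by 5 points (0.10 × 0.50) to 32 points (0.40 × 0.80). The difference is understated by r × b, which is 2 points (0.20 × 0.10) to 20 points (0.50 × 0.40).

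The direction does not depend on the assumptions chosen. The size depends almost wholly on the background rate, which the article does not give.

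**The case against.** The strongest reply is that this is a labelling slip with little consequence. Relationship and onset are recorded for every event, so a true treatment-related subset can be derived at any time. Section 8 of the full protocol may already define TRAEs by causality, and the analysis may follow it. That stands as a limit on the consequence, which holds only if the endpoint is analysed as 2.1 defines it. It does not excuse the sentence. The article states a definition and the definition is wrong. If Section 8 says otherwise, the two conflict.

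A second reply is that comparing all-cause events between randomized arms is sound. This also stands. Such a comparison validly estimates the all-cause excess. What is wrong is the treatment-related label, the incidence reported under it, and the use of a diluted any-event contrast as the measure of toxicity. Severity grade is also recorded and could sharpen the comparison.

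Some stronger readings are tempting but not supported:

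- A reader might infer that 2.17.2 contradicts the definition. It does not, because recording relatedness is compatible with counting all events. The contradiction lies within 2.1.
- A reader might infer that lingering complaints from the hepatectomy are all swept in. Only occurrences after consent are, so complaints that began before consent are not.
- A reader might infer that complications of the diagnostic angiogram certainly precede allocation. Sections 2.6 and 2.8 say so, but 2.9.1 leaves doubt.

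**Conclusion.** The definition in 2.1 is wrong as written for a key secondary safety endpoint. It describes all-cause adverse events under the name of treatment-related ones, and it starts the clock before allocation. Analysed as written, it would inflate the labelled incidence in both arms, dilute the contrast in the proportion with any event, and carry into the discontinuation endpoint.

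The illustrated range, an apparent difference of 27 down to 3 points for a 30% TACE-caused risk, rests on assumed rates and on independence. It shows direction and sensitivity and is not a prediction for this trial.

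A reader might conclude that the trial will misstate TACE toxicity, or that its safety assessment as a whole is compromised. The article does not support that. The analysis may follow a causality rule in a section not shown, SAE incidence does not use this definition, the raw data allow recovery, and the primary RFS analysis is untouched.

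**What to change.** Revise the definition in 2.1 as follows:

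1. Relabel the present definition as adverse event (AE).
2. Define a TRAE as an AE judged related to the randomized study procedure, using the relationship field in 2.17.2, with onset from the start of that procedure and the same attribution rule in both arms. Controls receive no agent, so state which time point marks the start for them.
3. Report all-cause AEs with onset after randomization as a separate line.
4. List events between consent and randomization separately, and report complications of the diagnostic angiogram as their own category in both arms. An onset rule tied to randomization cannot also capture angiography complications if the angiogram comes first, so these need their own line. Clarify the order of angiography and randomization in 2.9.1 at the same time.
5. Let the discontinuation endpoint use the revised term, and align all of this with Section 8 of the full protocol.

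The cost is a few sentences. Relationship and onset date are already recorded, so no new data are needed. Making the change before outcomes are known avoids having to choose later between an all-cause and a causal definition.
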